## Abstract

**Background:**

The objective of this study is to perform an independent evaluation of the feasibility and effectiveness of an educational programme for the primary prevention of type 2 diabetes (DM2) in high risk populations in primary care settings, implanted within the Basque Health Service - Osakidetza.

**Methods/design:**

This is a prospective phase IV cluster clinical trial conducted under routine conditions in 14 primary health care centres of Osakidetza, randomly assigned to an intervention or control group. We will recruit a total sample of 1089 individuals, aged between 45 and 70 years old, without diabetes but at high risk of developing the condition (Finnish Diabetes Risk Score, FINDRISC ≥ 14) and follow them up for 2 years. Primary health care nursing teams of the intervention centres will implement DE-PLAN, a structured educational intervention program focused on changing healthy lifestyles (diet and physical activity); while the patients in the control centres will receive the usual care for the prevention and treatment of DM2 currently provided in Osakidetza. The effectiveness attributable to the programme will be assessed by comparing the changes observed in patients exposed to the intervention and those in the control group, with respect to the risk of developing DM2 and lifestyle habits. In terms of feasibility, we will assess indicators of population coverage and programme implementation.

**Discussion:**

The aim of this study is to provide the scientific basis for disseminate the programme to the remaining primary health centres in Osakidetza, as a novel way of addressing prevention of DM2. The study design will enable us to gather information on the effectiveness of the intervention as well as the feasibility of implementing it in routine practice.

**Trial registration:**

ClinicalTrials.gov NCT01365013

## Background

Type-2 diabetes (DM2) has become one of the main causes of morbidity and early mortality in most countries, associated especially with a higher risk of cardiovascular diseases. Further, it is expected that the prevalence of DM2 will double by 2030 and that this condition will become the seventh cause of death worldwide [1]. Cardiovascular morbidity and mortality in individuals with DM2 is much higher than in the general population. The mortality rate associated with diabetes ranges between 13 and 30 deaths per 100,000 people per year, the main cause of death being coronary disease [2]. It has also been estimated that half of the population of Europe will have hyperglycaemia or diabetes during their lives [3], these conditions becoming more prevalent among both elderly and young people, with a sudden increase in those below 30 years of age [4]. This dramatic increase in the recently diagnosed cases of DM2 and its complications have become an important public health problem and affect almost all populations in both developed and developing countries [1,5].

In recent years, several clinical trials have demonstrated that is possible to prevent DM2 through educational interventions to change lifestyles. Specifically, in high risk subjects, the risk of developing DM2 can be reduced by around 60% after 3 years of these types of intervention [6-8]. Additionally, the effects of interventions focused on changing lifestyles seem to last in the long-term [9,10]. The findings of these studies are revealing. However, the evidence has been obtained from large controlled clinical trials, with well-developed infrastructure and considerable resources. It is not clear whether more realistic interventions, feasible under normal working conditions in health systems, would lead to results similar to those in the aforementioned large trials [11,12]. Therefore, the key question is: can the efficacy demonstrated in clinical trials be replicated in normal clinical working conditions, with much lower resources for the implementation of these types of programmes and interventions?

The step after testing the efficacy of a new experimental intervention, with phase III clinical trials, is the assessment of its effectiveness, efficiency and long-term sustainability under real conditions, with phase IV trials [13]. Unfortunately this step is not at all easy. The widespread adoption of this type of health intervention does not automatically follow from research proving its efficacy, let alone in the specific context of primary health care, characterised by work overload, with shortages of time and training. In recent years, there have been several initiatives assessing the transfer of interventions related to the promotion of healthy lifestyles for the prevention of DM2 to the real context of primary healthcare [14-20]. Some of these have indicated that it is feasible to reduce the risk of developing DM2 in several routine clinical settings. In most cases, however, the studies were not based on group comparisons, were not set up and implemented under real-world conditions in primary care settings or relied in additional resources, and/or did not include the reduction in the incidence of DM2 among the outcome variables. Despite evidence from experimental trials, the translation of lifestyle interventions into routine practice appears to have no effect on diabetes risk reduction [21].

Recently, *The Diabetes in Europe-Prevention using Lifestyle, Physical Activity and Nutritional Intervention* project (DE-PLAN), has been launched within the Spanish National Health Service [22]. This is a public health study focused on evaluating the implementation of a programme developed and implemented in the primary care setting involving: 1) a screening programme for identifying individuals at high risk of developing DM2; 2) an integrated programme with various different intensive interventions for changing lifestyles among high risk individuals; 3) an ongoing intervention programme for maintaining the motivation of participants; and 4) a programme for assessing the feasibility and cost-effectiveness of the aforementioned screening and intervention programmes, in different European primary care systems. The only results published so far concerning the DE-PLAN study conducted in Madrid are exclusively related to the participants in the intervention group, with no comparison group, so that the results obtained cannot be attributed to the programme [23]. One year after the intervention, about 7% of patients in the intervention group developed clinical features of DM2, similar to the figures reported for the control groups in two large DM2 prevention trials [6,7]. More recently, the researchers of the DE-PLAN project in Catalonia [24] have demonstrated that an intensive intervention for the promotion of healthy lifestyles is feasible in the context of primary care and does significantly reduce the prevalence of DM2 among high risk individuals. After a mean follow-up of 4.2 years, the incidence of DM2 was 7.2 and 4.6 cases per 100 people per year, for usual care and intensive intervention groups, respectively (equivalent to a 36.5% reduction in relative risk). In this study, patients were randomly selected previously to inclusion and centres were asked to assign subjects who agreed to take part in the programme consecutively to comparison groups if feasible. The fact that it is an observational study limits its ability to confirm the effectiveness of the programme in real-world primary care settings.

In short, the methodological limitations and mixed results of studies evaluating the effects of primary DM2 prevention programmes in primary care raise doubts as to whether the implementation of these programmes in normal working conditions in health centres would achieve the results observed in experimental trials. Accordingly, prior to widespread implementation, the transfer to real-word settings should be evaluated with a scientifically valid design. The transfer of effective and sustainable interventions to routine clinical practice remains one of the greatest challenges in scientific research in the field of DM2 prevention [12].

The “Prevention of Diabetes in Euskadi” project (PreDE) aims to perform an experimental evaluation of the implementation of a programme for the primary prevention of DM2, through the promotion of healthy lifestyles in patients at high risk of developing the disease, under normal working conditions in primary care. The project is based on the DE-PLAN programme and its methodology, though it has been adapted to the OSAKIDETZA centres. The primary objective is to assess the effectiveness and feasibility of the programme in the routine clinical practice of the centres and health professionals using an experimental a phase IV clinical trial design.

## Methods/design

### Objectives and hypothesis

#### Objectives

The general objective of the study is to perform an independent scientific evaluation of the impact of the implementation of an educational programme for the primary prevention of DM2 in high-risk populations seen in OSAKIDETZA primary care centres. This general objective can be broken down into several specific objectives:

i) to evaluate the results of the intervention programme in terms of reduction in the incidence of DM2, change in dietary habits, and increase in physical activity, among high-risk individuals attending OSAKIDETZA primary care centres in which the programme has been implemented.

ii) to estimate the effectiveness attributable to the intervention, comparing its results with those of patients seen in control centres where patients will receive the current usual care.

iii) to assess the feasibility of the intervention (in terms of coverage, adoption and implementation) in the OSAKIDETZA primary care centres.

#### Hypotheses

i) The implementation of a DM2 prevention programme based on an intervention to promote healthy lifestyles, physical activity and diet, carried out under normal working conditions in the primary care setting over a period of 12 months, will reduce the incidence of DM2 in high risk individuals by 50%, compared to that in a control group of high risk individuals who receive standardised usual care for the prevention of DM2. The expected reduction in the incidence, 50%, a clinically significant difference, is based on previous studies on DM2 prevention in other countries [6,7,24].

ii) In line with the DE-PLAN data from Spain [23], we expect that 50% of the patients exposed to the intervention programme will meet the recommended levels of physical activity (30 minutes of physical activity at least 5 times a week) and consumption of fruit and vegetables (at least 5 portions a day). In the control group, we expect that 25% of patients will meet the minimum recommendations.

### Study design

This is a phase IV randomized cluster clinical trial conducted in 14 Osakidetza primary care centres, randomly assigned to the intervention or control groups. The same system for identifying high-risk patients will be set up in all the centres, based on the administration of the 8-item Spanish version of the validated European Finnish Diabetes Risk Score (FINDRISC) [25]. Non-diabetic patients aged between 45 and 70 years old who are identified as at high-risk of developing DM2 (FINDRISC score ≥14) will be invited to participate in a follow-up programme lasting 24 months with annual medical check-ups. Additionally, a sub-sample of included patients will complete an independent, telephone interview carried out by blind external interviewers on dietary habits and level of physical activity at baseline and again after 12 months.

Primary care nursing professionals from the seven intervention centres have set up the DE-PLAN programme (for the intervention groups, IGs), adapted to the setting and normal working conditions in the health centres in OSAKIDETZA. Patients found to be at high risk of developing DM2 (FINDRISC score ≥ 14) who then complete the baseline assessments at these intervention centres will be invited to participate in the DE-PLAN programme; while those in the control health centres, will receive usual care for the prevention and treatment of DM2 (Figure 1).

**Figure 1 F1:**
[figure not shown]
Flow of the study.

#### Setting

The PreDE initiative is one of the strategic projects of the “Strategy for Tackling the Challenge of Chronicity in the Basque Country” of the Department of Health of the Government of the Basque Country [26]. This Department decided to commission a pilot study of the implementation of the DE-PLAN programme in 14 primary care centres of OSAKIDETZA and fund an independent assessment of the results, to provide a basis for its future dissemination to the remaining primary care health centres, as a new approach to the prevention of DM2 in the Basque Country. This protocol concerns to the design of the independent scientific assessment of the implementation of this prevention programme for diabetes under normal clinical conditions in the OSAKIDETZA primary care centres. The research protocol has been approved by the Basque Country Clinical Research Ethics Committee (Ref. no.: 10/2010). The Basque Healthcare Service (Osakidetza) provides universal free coverage, aside from co-payment for drugs, funded through regional general taxation. In Spain healthcare is a constitutionally-guaranteed right, the public system dominates the healthcare market and primary care services are almost exclusively supplied in public facilities. Each citizen is included in the list of one family physician or pediatrician who offers comprehensive primary care and constitutes the access gate by referral to hospital services. Primary care professionals work in full-time primary health care teams, including family physicians, pediatricians, nurses, and administrative staff hosted in centers and serving with extensive accessibility to a defined geographical area. Healthcare professionals have a civil-servant type labor status and they are paid a fixed salary with a small capitation supplement for physicians.

#### Participants

##### Primary care centres

In each of the seven health regions in which the Basque Health Service is organized, we selected a convenience sample of two centres, similar in terms of structure and population covered. After explaining the objectives of the project and working plan in a presentation session in each of the candidate centers, those professionals who wanted to collaborate signed a written commitment form individually. The 14 centres have been randomly assigned to the intervention and control groups, stratified on a 1:1 basis for each health region, using computer-generated random numbers provided by the Primary Care Research Unit of Bizkaia, such that in each health region there is one intervention and one control group.

##### Primary healthcare users

All users aged between 45 and 70 years old, without diabetes, who attend one of the participating health centres for any reason case during the period of implementation of the programme are eligible to participate. Exclusion criteria are: Previous diagnosis of diabetes mellitus other than gestational; To participate regularly in vigorous exercise programs; Having a chronic disease that makes survival at 6 years unlikely; Patients with diseases that could interfere with the metabolism of glucose.

#### Recruitment process

The 14 centres will implement a system for identification and screening of all eligible patients based on the FINDRISC scale. Eligible individuals with no exclusion criteria who have a score ≥ 14 on the FINDRISC scale, indicating that they are at high risk of developing DM2, will be invited to participate in the study and given the patient information sheet. This explains that they will be followed-up for a period of 24 months with annual medical check-ups consisting of blood lipid profile and glucose tolerance tests. In addition, to those belonging to intervention centres it provides information on the intervention protocol. Patients who agree to participate and sign an informed consent form, will be invited to perform an oral glucose tolerance test (OGTT) with 75 g of glucose in accordance with the WHO guidelines and a determination of lipid profile and HbA1C. Centre’s nurses will measure body weight, height, and waist circumference. Patients who after the test are diagnosed with DM2 will be seen by their family physician and excluded from the study. High-risk patients with glucose levels below 200 mg/ml in the OGTT will be included in the study.

A sub-sample of consecutive included patients once a full implementation of the program in centres is guaranteed (e.g., three months after study initiation), will undergo an independent baseline assessment by blind certified interviewers of their dietary habits and level of physical activity. In order to minimise selection bias, interviewers will make up to six telephone calls at different times of day and on different days in the week in an attempt to contact these individuals, until they are interviewed or are classified as “not contactable”. Non-contactable patients will not be substituted.

#### Intervention standardisation

##### Common treatment for both groups in the study

Both comparison groups will implement the same procedures for screening and initial assessment (clinical examination, blood lipid analysis, and an OGTT with 75 g of glucose, following the WHO guidelines) as well as annual check-ups at the health centres.

##### DE-PLAN educational intervention group

The DE-PLAN educational intervention programme for promoting healthy lifestyles (mainly diet and physical exercise) is carried out by nurses. The intervention is designed to achieve at least three out of the five following objectives: 1) maintenance of ideal body weight in people with normal weight and loss of >5% of body weight in those who are overweight or obese; 2) fat intake <30% of the daily energy intake, 3) intake of saturated fats <10% of the daily energy intake, 4) intake of fibre >15 g/1000 kcal/day, and 5) physical activity >4 hours per week. The intervention is performed in two phases:

a) Intensive intervention through educational sessions in small groups on the modification of unhealthy and adoption of healthy habits. This phase comprises four group sessions of 1.5 hours each. Its objective is to motivate participants to adopt healthy lifestyle habits and provide information concerning the most suitable diet and exercise, as well as agreeing on specific objectives for eating habits and physical activity.

b) Continuous reinforcement for maintaining motivation through regular contact with participants. Once the intensive education intervention programme has been completed, the participants will regularly (at least once every 6 weeks) receive reinforcing educational information via telephone calls, e-mails, etc. from nurses through a health communication platform.

The nurses in charge of the intervention group have received a 14-hour training course focused on the content and procedures for the educational intervention. Additionally, they have received a five-hour training course on the procedures for screening and identifying patients.

##### Control group

The nurses in charge of the control group will continue the current practice and provide the usual care with advice on healthy habits as part of the prevention and treatment of DM2, based on the current clinical practice guidelines of Osakidetza. Given that the system for screening and identifying patients is the same in both groups, the healthcare professionals of the control groups also received the five-hour training course.

#### Evaluation of results

##### Effectiveness of the intervention among patients

The primary outcome variable will be the relative risk of developing DM2, comparing the accumulated incidence (assessed by the OGTT) in the intervention and control groups after 24 months. The secondary outcome variables will be observed changes at 12 months in a sub-sample of intervention and control patients in: the proportion of patients who meet the recommended aerobic physical activity levels (moderate-intensity physical activity for ≥ 30 minutes 5 days/week or vigorous intensity activity for ≥ 20 minutes 3 days/week), derived from the 7-day Physical Activity Recall questionnaire [27]; and the proportion of patients who consume ≥ 5 servings of fruits and vegetables, assessed by the Mediterranean Diet Adherence Screener (MEDAS) used in the ‘*Prevención con Dieta Mediterránea* (PREDIMED)’ study [28]. Lastly, potential effect-modifying variables will be also measured: age, sex, and level of education, among others.

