#### Sample size

Considering the most conservative results found among high-risk patients in DM2 prevention projects in other countries [6,7] and the most recent data reported from the DE-PLAN project in Catalonia [24], the expected two-year incidence is 15% in the control group. Assuming that the percentage of people diagnosed with DM2 at 24 months will be 15% and 7.5% in the control and experimental groups respectively, and assuming a proportion of 60% recruited patients in the control group with respect to the total sample, to achieve a power of 80% to detect a 50% reduction in the incidence of DM2 as significant, by a Chi square test for independent samples with a two-sided p < 0.05, we need a recruitment under routine conditions of 355 and 237 patients in the control and intervention centres, respectively. However, if we assume that 15% of participants were to be lost to follow-up and an intra-class correlation of 0.01, given that this is a cluster-randomised clinical trial, the number of patients required would be 653 in the control group and 436 in the intervention group, that is, 1089 in total. A sample of 360 patients, 180 in each comparison group, will provide a statistical power of at least 90% to detect, as significant with p <0.05, differences of 50% in the percentage of patients who follow the minimum recommendations of physical activity and servings of fruit and vegetables.

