#### Analysis

Statistical analysis will be carried out using the SAS package (version 9.2; SAS Institute, Cary, NC; 2008). The percentages of diagnosed diabetes at 12 and 24 months after the inclusion in the study will be calculated and the level of association with exposure to the educational intervention, considering the potential confounders, will be assessed. Multiple logistic regression analyses will be performed on the percentage of patients diagnosed of diabetes at 24 months, adjusting for intervention group, socio-demographics (age, sex, etc.), and baseline clinical variables (BMI, BP, lipid profile values, etc.). Odds ratios (ORs) and the corresponding 95% confidence intervals (CIs) will be calculated.

Survival analysis will be used to compare the time until diagnosis of diabetes in the different groups. To assess the univariate association of the time until diagnosis of diabetes with the comparison groups and with other possible predictors, cumulative survival probabilities in the 24 months will be estimated and compared using Kaplan-Meier curves along with the log-rank and Wilcoxon tests (SAS PROC LIFETEST, version 9.2, SAS Institute; 2008). Person-years will be the sum of time under follow-up for all participants before diabetes diagnosis or end of follow-up if free of developing diabetes. Subjects who withdrew from the study will be considered to be at risk for diabetes until their last oral glucose tolerance. However, an effort will be made in order to ascertain a diabetes diagnosis at the end of the study period reviewing patients’ charts. Adjusted hazard ratios (AdHRs) and 95% CIs will be estimated to compare diagnosis of diabetes risks between patients in different groups using Cox proportional hazards models introducing all the variables studied in the bivariate analysis as potential confounders. The proportional hazard assumption will be assessed using graphical techniques and a statistical test based on Schoenfeld partial residuals of the model. In the case of covariates for which the proportional hazard assumption is not satisfied, the Cox model will be extended with time-dependent variables allowing hazard ratios to change over time. Finally, to model the clustered structure of data, a common random effect will be introduced into the Cox’s proportional hazards model. This estimation will be carried out by adaptive Gaussian quadrature method implemented in SAS PROC NLMIXED.

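### The primary outcome is a 24-month relative risk, but the Analysis section specifies no relative risk with a confidence interval and names no primary analysis

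*Protocol article*

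**What the plan says.** In the section Effectiveness of the intervention among patients, the article states: "The primary outcome variable will be the relative risk of developing DM2, comparing the accumulated incidence (assessed by the OGTT". The two arms are compared at 24 months. The Hypotheses section expects incidence to be halved, and the Sample size section takes 15% and 7.5% at 24 months and sizes the trial "by a Chi square test for independent samples with a two-sided p < 0.05".

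For diabetes, the Analysis section lists the following:

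- Description: "The percentages of diagnosed diabetes at 12 and 24 months after the inclusion in the study will be calculated".
- A binary model: "Multiple logistic regression analyses will be performed on the percentage of patients diagnosed of diabetes at 24 months", adjusted for socio-demographic and baseline clinical variables. Its output is fixed: "Odds ratios (ORs) and the corresponding 95% confidence intervals (CIs) will be calculated". No centre term is mentioned.
- Time to diagnosis: cumulative survival probabilities, "compared using Kaplan-Meier curves along with the log-rank and Wilcoxon tests".
- Cox regression: "Adjusted hazard ratios (AdHRs) and 95% CIs will be estimated to compare diagnosis of diabetes risks". As a last step, a common random effect is added to the Cox model to represent the clustering.

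None of these is called primary. The chi-square test used for sizing is not listed for diabetes; in the analysis text it appears only for secondary proportions.

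**The concern.** The endpoint, the hypothesis and the sample size are all on the risk scale. The effect measures named in the Analysis section are on the odds and hazard scales. The declared quantity therefore has no planned interval, no planned adjustment and no planned allowance for centre.

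Two things are at stake. First, the hypothesised halving of incidence is not what an odds ratio or hazard ratio measures, and the trial is meant to inform a region-wide roll-out, where risks are the natural currency. Second, the listed analyses treat the 14 randomised centres differently. If the text does not say which one decides the hypothesis, it does not say whether the deciding result respects the cluster randomisation.

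**Working it through.** **Inputs.** From Sample size: p0 = 0.15 (control), p1 = 0.075 (intervention), 60% of patients in control (intervention-to-control ratio k = 2/3), 80% power, two-sided 0.05, ICC 0.01, 15% loss, 653 + 436 = 1089 recruited. From Study design and Participants: 14 centres, seven per arm.

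**1. The article's own figure.** Use the pooled-variance chi-square formula without continuity correction. The pooled risk is 0.6 × 0.15 + 0.4 × 0.075 = 0.12, and

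n(control) = [1.96 √(0.12 × 0.88 × (1 + 1/k)) + 0.842 √(0.15 × 0.85 + 0.075 × 0.925/k)]² / 0.075² = 354.5.

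The intervention arm needs 354.5 × 2/3 = 236.3. Rounded up, these are the stated 355 and 237. The trial is therefore sized for a comparison of two 24-month risks.

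**2. One effect on three scales.**

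- RR = 0.075/0.15 = 0.50
- OR = (0.075/0.925)/(0.15/0.85) = 0.459
- HR = ln(0.925)/ln(0.85) = 0.480, assuming proportional hazards

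Read as a risk reduction, the odds ratio gives 1 − 0.459 = 54% against a true 50%. If the control risk were between 10% and 20% with RR still 0.50, the OR would run from 0.474 to 0.444 and the HR from 0.487 to 0.472.

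**3. The gap against the expected precision.** Evaluable patients: 653 × 0.85 = 555 and 436 × 0.85 = 371, or about 66.1 per centre if centres are equal in size (an assumption). The design effect is 1 + (66.1 − 1) × 0.01 = 1.65.

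SE(ln RR) = √{1.65 × [0.925/(0.075 × 371) + 0.85/(0.15 × 555)]} = 0.268.

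The expected 95% intervals are RR 0.50 (0.30 to 0.85) and, by the corresponding formula, OR 0.46 (0.26 to 0.82). The difference of 0.04 between the point estimates is small beside either interval. These intervals use 1.96 and no small-sample correction, so they are slightly optimistic.

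**4. Which routes account for centre.** As the text stands:

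- Logistic model: no centre term stated.
- Log-rank and Wilcoxon: no centre term stated.
- Cox model with covariates: no centre term stated.
- Cox model with random effect: clustering modelled.

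**5. What the choice of route does to type I error.** A null simulation covered three unadjusted tests: chi-square, log-rank and Wilcoxon. Assumptions: 15% risk in both arms, visits at 12 and 24 months, half of the events by 12 months, 10% loss between visits, beta-binomial clustering, region strata ignored, 10,000 runs per setting.

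| Setting | Each test rejects | Any of the three rejects |
|---|---|---|
| No clustering, N = 592 or 926 | about 5% | 5.7% |
| ICC 0.01, N = 592 | about 9% | 9.8% |
| ICC 0.01, N = 926 | about 12% to 12.5% | 13.7% |

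The three tests are highly correlated, so choosing among them adds little. Leaving out the centre effect adds much more. The covariate-adjusted models were not simulated.

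**The case against.** A fair defence has four parts.

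- **The relative risk can be obtained.** A reader might infer that the declared quantity is never estimated. The text does not support that: the 24-month percentages and the Kaplan-Meier probabilities each yield two cumulative incidences, and their quotient is a crude relative risk. This part stands. What is missing is an interval for that ratio and any adjusted or clustered version of it.
- **Multiple tests.** A reader might also infer that several tests at 0.05 seriously inflate the false-positive rate through selection. The simulation does not bear this out: 5.7% for any of three against about 5% for each. This part stands too.
- **The analyses form a sequence.** The survival analyses move from univariate to adjusted to cluster-adjusted, and a condensed article may leave the label of primary to its analysis plan. This stands in part. The missing label alone would be weak ground. But the article does fix its effect measures in detail, and they are not the one it declares as its outcome. That is a mismatch between two stated parts of one document.
- **The numbers are close and honestly labelled.** The outputs are called odds ratios and hazard ratios, and nothing proposes reading them as relative risks. The Background also applies the term relative risk to a reduction in person-year rates, so the authors may use it loosely. This limits the size of the point. It does not remove it, because the outcome definition refers explicitly to cumulative incidence at 24 months.

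**Conclusion.** The point holds as an inconsistency between the outcome definition and the Analysis section. The declared primary quantity has no planned confidence interval, and no listed analysis is named as the one that decides the hypothesis.

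The scale effect is modest: RR 0.50 against OR 0.459 and HR 0.480, which matters only if an odds or hazard ratio is read as a risk ratio. The OR figure rests on the article's 15% and 7.5%; the HR figure also assumes proportional hazards. The odds ratio from the planned model is also conditional on its covariates, which can move it further from the risk ratio; the documents give no basis for putting a figure on that.

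The more important consequence is that the routes differ in whether they respect the 14 centres. At the article's own ICC of 0.01, an unclustered test at the evaluable planned size rejected a true null in about 12% of simulated trials, under the assumptions listed. This does not mean that the final analysis will ignore clustering, since the random-effect Cox model is planned. It means that the text does not commit to that model, and that the model does not give the declared measure. The sample size calculation is not affected by this point.

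**What to change.** In the Analysis section, name one primary analysis: the 24-month risk ratio, with the risk difference, and a 95% interval that allows for clustering by centre and includes a small-sample correction for 14 centres. Either of two routes gives this:

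- a modified Poisson or log-binomial model with centre clustering; or
- marginal standardisation from a logistic model with a random intercept for centre.

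Label the odds ratios, the log-rank and Wilcoxon tests and the Cox results as supportive.

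The alternative is to keep the survival approach and restate the primary measure, where the outcome is defined, as the hazard ratio from the random-effect Cox model. The hypothesised effect should then be given on that scale as well (HR 0.480 for 15% v 7.5% under proportional hazards).

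The cost is wording and a few lines of code. No new data are needed.
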